### Analytical plan

2.8

Survey-Study 1: We will examine the prevalence rates of insomnia (continuous and categorical dimensions), disrupted sleep continuity, physical activity, psychological well-being, including depression, anxiety, stress, coping with stress, emotion regulation, concentration, social activity, and mental toughness. A series of Pearson’s correlations are run to calculate the associations between the variables mentioned above. Chi-square-tests will be used to calculate the associations between categorical dimensions. To explore which psychological dimensions are statistically more strongly associated with insomnia, we run regression analyses; the minimum requirements are as follows (137, 144, 145): *N* = x > 100; predictors explain the dependent variables (R > 0.40, R^2^ > 30); the number of predictors x 10 should be < N; the Durbin–Watson coefficients should be between 1.5 and 2.5, indicating that the residuals of the predictors are independent. For the variances inflation factors (VIF): While there are no strict cut-off points to report the risk of multicollinearity, VIF < 1 and VIF > 10 indicate multicollinearity.

For t-tests, Cohen’s d effect sizes are reported with the following cut-off values: Trivial (ds: 0–0.19), small (ds: 0.20–0.49), medium (ds: 0.50–0.79) or large (ds: 0.80 and greater) (146–148).

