### Participants

2.1

We expect that all 480 MDs of the SAF complete the survey. The inclusion criteria are: 1. Aged 18 years and older; 2. Master degree or higher in human medicine; 3. MD of the SAF; 3. Willing and able to comply with the study conditions; 4. Signed written informed consent. Exclusion criteria are: 1. Completing the questionnaires in an unreliable fashion (“clickthroughts”; answers are given clicking systematically on the right or left side or in the middle; questionnaires are completed within a couple of minutes). 2. A participant withdraws from the study. 3. Pregnancy or breastfeeding, as this may alter sleep and psychological well-being. 4. A participant leaves the SAF.

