### Limitations

3.2

We are aware of the following study limitations. First, all data are self-reported, and as such, biases in the self-perception cannot be ruled-out. Ideally, psychiatrists and clinical psychologists would run clinical interviews to assess possible psychiatric disorders (155, 156). Second, we assess sleep disturbances, including psychological well-being both in a participants’ military and family/private/professional context: While the unique structure of SAF military service, including repeated regular training courses over several years, helps to keep an expert’s specific military skills high, the boundaries between civil/professional and military life might get blurred, with quick and sometimes unpredictable transitions from civil life to military deployments and vice versa. As such, it might be challenging to complete the questionnaires, while cognitively discerning between civil/professional and military life. Third, given the strictly voluntary character of both the survey and the intervention and considering a MD’s workload, it is not clear, how many military medical doctors will participate. Fourth, very similar to the literature on sleep disturbances among military personnel and military MDs (see Introduction section), we mainly assess insomnia and disrupted sleep continuity, while further sleep disturbances such as Restless Legs Syndrome (RLS), Obstructive Sleep Apnea (OSA), parasomnias, including night terrors and night mares are not considered. However, one paragraph in the survey asks more specifically about sleep-impairing events; as such, participants could report sleep-issues such as RLS, OSAs, and parasomnias. Fifth, we focused prevalently on sleep quality (insomnia), while sleep quantity (disrupted sleep continuity such as delayed sleep onset latency and awakenings after sleep onset) was regarded as less important (157).

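### The minimum-fit requirement for the exploratory Survey-Study 1 regressions (R > 0.40, R² > 30) is wrong as written: its two limits do not match, and fit is a result, not a precondition

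*Protocol article*

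**What the plan says.** In the protocol article, section 2.8 (Analytical plan), the regression serves an exploratory purpose: "To explore which psychological dimensions are statistically more strongly associated with insomnia". It is introduced with "we run regression analyses; the minimum requirements are as follows", and a list follows:

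- a sample size above 100;
- a minimum fit: "predictors explain the dependent variables (R > 0.40, R^2^ > 30";
- a predictor limit: "the number of predictors x 10 should be < N";
- a Durbin-Watson coefficient between 1.5 and 2.5, "indicating that the residuals of the predictors are independent".

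On collinearity the section adds that "VIF < 1 and VIF > 10 indicate multicollinearity".

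The article does not say what happens to a model that misses a requirement, and it does not give the number of predictors. On sample size, section 2.1 states "We expect that all 480 MDs of the SAF complete the survey", while the Limitations concede that "it is not clear, how many military medical doctors will participate".

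**The concern.** The list mixes two kinds of condition. Sample size and the predictor limit can be checked before fitting. R and R² are known only afterwards, and they are part of the answer. A weak overall association between psychological well-being and insomnia would be a valid finding for a survey whose second aim is the pattern of associations. A minimum on fit treats that finding as a failed precondition.

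The fit rule is also faulty in itself. One half cannot be met as printed, and under the obvious repair the two halves set different limits. An analyst whose model falls between them cannot tell from the text whether it qualifies. If the rule were used to decide which models are reported, the published R² would come from a sample selected for good fit.

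**Working it through.** **Inputs.** The limits on R and R², the N > 100 rule and the predictor rule come from section 2.8. The upper bound of N = 480 comes from section 2.1. Two inputs are assumptions: 10 predictors, and true R² values from 0 to 0.40. Ten is the most that the predictor rule allows at N = 101 (10 × 10 = 100 < 101); at N = 480 it would allow 47 (470 < 480).

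**Step 1: do the two limits agree?** For one model, R² = R × R.

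- R > 0.40 gives R² > 0.40² = 0.16.
- R² > 0.30 gives R > √0.30 = 0.548.
- R² > 30 has no solution, because R² cannot exceed 1.

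The stated pair is therefore not reproduced. Adjusted R², 1 − (1 − R²)(N − 1)/(N − p − 1), does not rescue it. At R = 0.40 with p = 10 it is 1 − 0.84 × 100/90 = 0.067 for N = 101, and 1 − 0.84 × 479/469 = 0.142 for N = 480.

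**Step 2: how often would a model fall between the limits?** Sample R² was simulated for multivariate normal predictors, with at least 100,000 draws per setting. With a true R² of 0.20, the share with R > 0.40 but R² ≤ 0.30 is 59% at N = 101, 74% at N = 150 and 95% at N = 480.

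**Step 3: what would reporting only the passing models do?** The mean R² of all models is the baseline, because sample R² already exceeds the true value through ordinary overfitting.

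| N | True R² | Filter | Mean R², all models | Share passing | Mean R², passing models | Added by filter |
|---|---|---|---|---|---|---|
| 101 | 0.20 | R² > 0.30 | 0.277 | 37% | 0.352 | 0.075 |
| 150 | 0.20 | R² > 0.30 | 0.252 | 21% | 0.335 | 0.083 |
| 200 | 0.20 | R² > 0.30 | 0.239 | 12% | 0.326 | 0.087 |
| 480 | 0.25 | R² > 0.30 | 0.265 | 15% | 0.318 | 0.053 |
| 480 | 0.30 | R² > 0.30 | 0.314 | 65% | 0.334 | 0.020 |
| 101 | 0.40 | R² > 0.30 | 0.456 | 98% | 0.459 | 0.003 |
| 150 | 0.10 | R > 0.40 | 0.159 | 47% | 0.202 | 0.043 |
| 480 | 0.20 | R > 0.40 | 0.216 | 96% | 0.219 | 0.003 |

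**Step 4: the other two diagnostics.** VIF for predictor j is 1/(1 − R²ⱼ), where R²ⱼ comes from regressing predictor j on the others. Since 0 ≤ R²ⱼ < 1, VIF is at least 1, and the lower limb can never apply.

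The Durbin-Watson statistic is Σ(eₜ − eₜ₋₁)²/Σeₜ², so it compares residuals of neighbouring rows. Survey respondents have no natural order and re-sorting the file changes the value, so a result within the range does not show independence. The residuals also belong to the fitted model, not to the predictors.

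**The case against.** Four points can be made in the plan's defence.

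- A reader might infer that the two limits contradict each other. They do not: any model with R² > 0.30 also has R > 0.40, so both can hold. Read as a joint list, the rule reduces to R² > 0.30. This stands. The limits are mismatched and one is redundant.
- A reader might infer that the survey models will overstate fit. The article does not support that, because it never says that models below the limit are withheld, refitted or left uninterpreted. This also stands, so the bias can only be stated conditionally.
- A reader might infer that a weakly related dimension would disappear from the results. The requirement applies to the whole model, so a weak predictor in a passing model is still shown. Section 2.8 also plans Pearson correlations among the same variables with no fit condition, so the aim on patterns of association does not rest on the regressions alone.
- The missing decimal or percent sign after R² may be a typing or text-conversion slip, and the impossible VIF limb does no harm because it never triggers. Both are fair, but correcting the slip leaves the mismatch of Step 1 in place.

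The defence does not explain why a minimum fit should be a requirement at all.

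**Conclusion.** The concern holds as a minor fault confined to the exploratory Survey-Study 1 regressions. The fit requirement is wrong as printed, inconsistent as one threshold when repaired, and misplaced among preconditions.

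Any effect on reported R² depends on two things: that failing models go unreported, and that the true R² is near or below the cut-off. In the settings shown with a true R² of 0.20 to 0.25, the filter at R² > 0.30 adds about 0.05 to 0.09; at a true R² of 0.40 its effect is negligible. These sizes rest on the assumed 10 predictors and on normal data.

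It would be tempting to say that the rule doubles the apparent fit, since at N = 150 and a true R² of 0.10 the passing models average 0.202. Most of that excess is ordinary overfitting: 0.059 arises without any filter, and 0.043 comes from the filter.

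The Pearson correlations, the randomised comparison and its sample size are unaffected.

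**What to change.** In section 2.8:

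1. Delete the requirement on R and R².
2. State that every planned regression meeting N > 100 and 10 × predictors < N will be reported, with R², adjusted R² and confidence intervals for the coefficients, whatever its fit.
3. State the collinearity rule as VIF > 10 only.
4. Drop the Durbin-Watson criterion, or replace it with residual plots.

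The cost is wording only, with no new data or analyses. Some reported R² values may be less favourable than under a selective rule.

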#### Intervention

2.8.1

ANOVAs for repeated measures are run with the factors Group (eCBTi vs. ACC), Time (baseline, week 3, week 6), and the Group x Time-interaction; dependent variables as reported in Table 2. Post-hoc analyses after Bonferroni-Holm are used for p-corrections for multiple testing. Single mean comparisons are performed with Cohen’s d effect sizes, as proposed by Becker (149). In case of missing values, such missing data will be replaced with the means or medians of the sample (144, 145, 150, 151). For the intervention study: Statistical procedures are run both by protocol (that is: only available data observed at any time point from every participant are considered) and by intent-to-treat (ITT) with the last intervention carried forward (LOCF) (152). Further, we consider the following confounders, that is to say, we statistically calculate, whether the pattern of results might get biased in the same or opposite directions for the following confounders: Age, gender, working condition, including current full time or part time positions as medical doctors, including their subspeciality such as neurosurgeon, anesthesiologist, or emergency MD, to name but a few, and military rank, or time lapse between the assessment and the last deployment.

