**Expected outcomes:**

Survey-Study 1: We expect to describe the prevalence rates of, and the associations between sleep disturbances (insomnia (sleep quality); sleep onset latency (SOL); awakenings after sleep onset (WASO)) and psychological well-being among MDs of the SAF; we further expect to identify specific dimensions of psychological well-being, which might be rather associated or non-associated with sleep disturbances.

Intervention-Study 2: We expect several significant condition-by-time-interactions. Such that participants in the eCBTi will report significantly greater improvement in sleep disturbances, symptoms of depression, anxiety, stress reduction both at work and at home (family related stress), and an improvement in the overall quality of life as compared to the ACC over the period of the study.

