**Conclusion:**

The study offers the opportunity to understand the prevalence of sleep disturbances, including factors of psychological well-being among MDs of the SAF. Further, based on the results of the Intervention-Study 2, and if supported, eCBTi may be a promising method to address sleep disturbances and psychological well-being among the specific context of MDs in the SAF.

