### The present study

1.7

Overall, there is sufficient evidence that compared to non-military personnel, military personnel report more impaired sleep, along with more issues of psychological well-being. This holds particularly true for MDs in the military context, though, research on this topic is scarce. More specifically, for MDs of the SAF, no research is available on the prevalence and association of sleep disturbances, along with concomitant issues of psychological wellbeing.

Given this background, the present study has the following aims:

Survey-Study 1: (1) To investigate the prevalence of sleep disturbances (insomnia; disrupted sleep continuity), and concomitant issues of psychological well-being among MDs of the SAF. (2) To investigate the patterns of associtions between sleep disturbances and issues of psychological well-being; (3) to identify MDs who report sleep disturbances (insomnia severity index >8), along with further dimensions of psychological ill-being and well-being such as symptoms of depression, anxiety, stress, emotion regulation, concentration, social activity, strengths and difficulties and mental toughness.

Intervention-Study 2: (3) To offer a stanrdardized online CBT program for insomnia (eCBTi). To this end, MDs reporting sleep disturbances will be randomly assigned either to the internvention condition (see details below) or to the active control condition (see details below).

For the Survey-Study 1, the hypothesis is: Higher scores for sleep disturbances are associated with more issues of psychological wellbeing such as depression, anxiety, and stress, including also social behavior.

For the Intervention-Study 2, the hypothesis is: Compared to the baseline and to an ACC, at the end of the intervention participants of the eCBTi report improved sleep disturbances, along with improved psychological well-being, as mentioned above.

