### Measures

2.5

Survey-Study 1: Table 1 provides the overview of the study measures. The primary outcome measures are sleep disturbances (insomnia; sleep onset latency (SOL); awakenings after sleep onset (WASO) = disrupted sleep continuity). Secondary outcomes are psychological ill-being and well-being, including depression, anxiety, stress, coping strategies, emotion regulation, concentration, social activity, strengths and difficulties, and mental toughness.

Intervention-Study 2: Table 2 provides the overview of the study measures. Primary outcomes are change in sleep disturbances (insomnia; disrupted sleep continuity). Secondary outcomes are psychological ill-being and well-being, including the dimensions metioned above, and additionally: Sleep-related cognitions, experiential avoidance, and mindfulness self-awareness (see also Table 1).

**Table 2 tab2:** Elements of electronically delivered cognitive behavioral therapy for insomnia (eCBTi).

Session	Content
One	What is sleep? Provides an overview of the course and introduces the concepts of sleep, CBT, and insomnia.
Two	How various sleep habits impact on sleep. Provides stimulus control instructions, such as activities that are permitted or disallowed when in bed, daytime napping and what to do if sleep is not attained at night. Provides sleep restriction instructions, including setting specific bedtime, maintaining the same wake time, and restricting time spent in bed awake.
Three	Sleep hygiene education and discusses behavioral health practices, such as caffeine, alcohol, exercise, diet, smoking, and environmental factors’ impacts on sleep. Overview of relaxation techniques that support sleep.
Four	Role of automatic and negative thoughts and how they influence feelings. Identification of negative thoughts and alternative interpretations (cognitive restructuring)
Five	As session four; cognitive restructuring
Six	Review; summary of the main concepts of CBTi; what did I learn?

CBTi, cognitive behavioral therapy for insomnia.

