### Sample size calculations

2.7

To calculate the sample size for the intervention study, we used the G*Power software (143). Based on previous studies on the efficacy of eCBTi (86–92), we expect a partial eta-squared of 0.08 (medium effect); alpha: 0.05; Power: 0.95; number of groups: 2; number of measurements: 3; total sample size: 32, that is, 16 per condition. To counterbalance possible drop-out, we assess 25 participants per condition.

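### Bonferroni-Holm is tied to post-hoc analyses and not clearly to the Group x Time tests on about 13 to 20 secondary scores, yet the Study 2 hypothesis claims improved well-being from those tests

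*Protocol article*

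**What the plan says.** **Outcomes.** Section 2.5 makes the sleep measures primary in Intervention-Study 2. Of the rest it says: "Secondary outcomes are psychological ill-being and well-being, including the dimensions metioned above, and additionally: Sleep-related cognitions, experiential avoidance, and mindfulness self-awareness". The article gives no count of secondary scores.

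**Analysis.** Section 2.8.1 specifies repeated-measures ANOVAs with factors Group and Time and their interaction. For the dependent variables it points to Table 2, but Table 2 lists the content of the therapy sessions; the measures are in Table 1. The multiplicity rule follows directly: "Post-hoc analyses after Bonferroni-Holm are used for p-corrections for multiple testing". The sentence after it turns to single mean comparisons and Cohen's d.

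**Claims.** The Study 2 hypothesis (section 1.7) is that, compared with baseline and the control condition, "participants of the eCBTi report improved sleep disturbances, along with improved psychological well-being, as mentioned above". The abstract says "We expect several significant condition-by-time-interactions" and names depression, anxiety and stress among the outcomes expected to improve. Section 3.1.1 expects improvement on a long list of secondary dimensions. The abstract's conclusion is conditional: "if supported, eCBTi may be a promising method to address sleep disturbances and psychological well-being among the specific context of MDs in the SAF".

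**Alpha.** The figure 0.05 appears only in section 2.7: "we expect a partial eta-squared of 0.08 (medium effect); alpha: 0.05; Power: 0.95; number of groups: 2; number of measurements: 3; total sample size: 32".

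**The concern.** The stated correction and the stated hypothesis do not meet. In ANOVA usage, post-hoc analyses are the mean comparisons made after an omnibus test. On that reading Holm protects the contrasts within each outcome and leaves the set of secondary interaction tests without familywise control. Those interaction tests are what the well-being part of the hypothesis rests on, and the article does not say how many of them must be positive for that part to count as supported.

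At stake is a well-being claim built on whichever scales happen to cross 0.05. The ambiguity is also large. The first-step threshold for a secondary interaction is 0.05 on one reading and 13 to 19 times smaller on the other, and the choice could be made after the results are seen.

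**Working it through.** **1. The plan's own figure.** Inputs from section 2.7: partial eta-squared 0.08, alpha 0.05, power 0.95, 2 groups, 3 measurements. Not stated, so assumed: correlation 0.5 between repeated measures and sphericity.

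- f² = 0.08/(1 − 0.08) = 0.087, so f = 0.295.
- Noncentrality λ = f² × N × 3/(1 − 0.5); df1 = 2, df2 = 2(N − 2).
- N = 32: λ = 16.7, power 0.955. N = 30: power 0.941.

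The stated 32 is reproduced, for one interaction test at an unadjusted 0.05.

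**2. How many secondary tests.** Counted from section 2.5 and Table 1:

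- 13 constructs: depression, anxiety, stress, coping, emotion regulation, concentration, social activity, strengths and difficulties, mental toughness, dysfunctional sleep beliefs, bedtime procrastination, experiential avoidance, mindfulness.
- 14 if PHQ-9 depression and DASS-21 depression are counted separately.
- 19 scores if coping is also split in two and the SDQ into its five dimensions; 20 if emotion regulation is split in two.

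Section 2.5.1 mentions separate private/civil and military questionnaires under the online survey. If both are analysed in Study 2, the count rises further; that is not included below.

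**3. Error rate if each interaction is tested at 0.05.** The correlation ρ between outcomes is in no document; I assume equal correlation and vary it from 0 to 0.7. With c = 1.96 and k tests:

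- Either direction: 1 − ∫[Φ((c − √ρ·x)/√(1−ρ)) − Φ((−c − √ρ·x)/√(1−ρ))]^k φ(x)dx; for ρ = 0 this is 1 − 0.95^k.
- Benefit only: 1 − ∫[Φ((c − √ρ·x)/√(1−ρ))]^k φ(x)dx; for ρ = 0 this is 1 − 0.975^k.

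| ρ | 13, either direction | 13, false benefit | 19, either direction | 19, false benefit |
|---|---|---|---|---|
| 0 | 48.7% | 28.0% | 62.3% | 38.2% |
| 0.3 | 41.8% | 21.4% | 52.5% | 27.2% |
| 0.5 | 33.4% | 16.7% | 40.9% | 20.5% |
| 0.7 | 24.1% | 12.0% | 28.3% | 14.2% |

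A single test has a 2.5% chance of a false benefit, so the inflation runs from 12.0/2.5 ≈ 5-fold to 38.2/2.5 ≈ 15-fold. Counts of 14 and 20 give slightly higher rates (34.8% and 41.9% in either direction at ρ = 0.5).

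**4. Check on the F test itself.** The table uses a z approximation. Simulating the interaction F test with 25 per arm (6,000 null replicates, ρ = 0.5) gave 34.9% and 43.1% for 13 and 19 outcomes with three time points, and 33.3% and 41.4% with two. The two-time-point case matters because coping, emotion regulation, concentration, social activity, SDQ and mental toughness are measured only at baseline and week 6.

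**5. With Holm across the interactions.** First-step level: 0.05/13 = 0.0038; 0.05/19 = 0.0026. Simulated familywise error was 2.5-5.1% over ρ = 0 to 0.7. Power at that first step for the protocol's effect, under the assumptions of step 1:

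| N | 13 tests | 19 tests |
|---|---|---|
| 32 | 0.76 | 0.72 |
| 50 | 0.96 | 0.95 |

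These power figures apply to outcomes with three time points.

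**The case against.** **The unadjusted 5% is inferred.** No sentence says each secondary interaction is tested at an unadjusted 0.05. The Holm sentence directly follows the ANOVAs on all dependent variables and speaks of multiple testing, so it could be meant to cover them. This stands as a limit on the point: the text is ambiguous. The narrower reading is still the more natural one. The correction is attached to post-hoc analyses, the next sentence is about mean comparisons, and the sample size is computed for one test at 0.05.

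**A false benefit is not likely.** A reader might infer that a false well-being benefit has a 33-41% chance. The document does not support that. Those figures count significance in either direction and hold only at an assumed correlation of 0.5. In the favourable direction they are 17% and 20%.

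**One positive scale is not the protocol's criterion.** The abstract expects several significant interactions. At ρ = 0.5 the chance of at least two false benefits is about 7% (13 scores) to 10% (19), and of at least three about 4% to 6%. If the four added sleep-cognition, avoidance and mindfulness scales are left out of well-being, 9 constructs remain, with 27% in either direction and 13.5% for a false benefit. These figures are fair. They lower the size but leave the gap, because the article does not say what counts as support.

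**The claim is hedged, and detail may sit elsewhere.** The abstract's conclusion is conditional and does not recommend eCBTi outright. Ranking the secondaries, or choosing between PHQ-9 and DASS-21 depression, may be left to an analysis plan that is not shown, and I do not count either as a fault. What remains is that the article itself states both a multiplicity rule and a hypothesis, and the rule as worded does not clearly cover the hypothesis.

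**Conclusion.** The point holds as a mismatch between the stated correction and the stated hypothesis. It concerns the secondary outcomes only. On the most natural reading of section 2.8.1, the well-being part of the Study 2 hypothesis has no familywise error control. With 13 to 19 scores, the chance under the null of at least one significant secondary interaction in either direction is then 24-49% (13) or 28-62% (19). The chance of at least one false benefit is 12-38%, and 17% to 20% at correlation 0.5, against 2.5% for a single test. The inflation is material, but a false benefit is not the expected result.

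These sizes rest on three things the article does not give: a 0.05 level for each interaction, my count of scores, and the between-outcome correlation. If Holm was in fact meant to cover the secondary interactions, error is controlled and only the wording needs correcting.

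**What to change.** In section 2.8.1, choose one of two options and state it:

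1. Apply Bonferroni-Holm across the secondary Group x Time tests, and list the scores that form the family. The list should point to Table 1 instead of Table 2. The first-step level is about 0.0038 to 0.0026. For the assumed effect, power there stays about 0.95 if all 50 participants are analysed, but falls to 0.72-0.76 if only 32 remain.
2. State that the confirmatory claim is for the sleep outcomes only, and report all secondary outcomes as exploratory estimates with 95% confidence intervals.

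Then bring the well-being wording in the abstract (expected outcomes and conclusion) and in section 1.7 into line with the choice.

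The cost is a change of wording, with no new data. The downside is that an isolated positive secondary scale can no longer be reported as a confirmed effect.

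### Mean/median replacement has no stated scope and LOCF is the only ITT method; applied to missed visits, each can distort the eCBTi–ACC comparison or its standard error

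*Protocol article*

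**What the plan says.** All the relevant text is in section 2.8.1 (Intervention) of the protocol article.

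- **Model:** "ANOVAs for repeated measures are run with the factors Group (eCBTi vs. ACC), Time (baseline, week 3, week 6), and the Group x Time-interaction".
- **General rule for missing values:** "In case of missing values, such missing data will be replaced with the means or medians of the sample". The sentence does not say whether it covers whole missed assessments or single questionnaire items, whether the sample is both arms together or each arm, or when a mean and when a median is used.
- **Two analyses of the intervention study, in the next sentence:** one is labelled by protocol and defined by the condition that "only available data observed at any time point from every participant are considered". The other is run "by intent-to-treat (ITT) with the last intervention carried forward (LOCF". The expansion of the abbreviation speaks of the last intervention, where the last observation must be meant.

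Section 2.7 sets the size at "alpha: 0.05; Power: 0.95; number of groups: 2; number of measurements: 3; total sample size: 32, that is, 16 per condition", and then: "To counterbalance possible drop-out, we assess 25 participants per condition". No dropout rate is given. Section 2.5 names change in sleep disturbances as the primary outcome.

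**The concern.** The replacement rule and the two analyses do not fit together unless the rule's scope is known. If missed visits were filled with means or medians first, LOCF would have nothing to carry forward and the available-data set would no longer differ from the full set.

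The methods are also weak in themselves if used on missed visits. Mean or median filling and LOCF are single imputations: they put one fixed value in place of an unknown one and then analyse it as if it had been measured. LOCF further assumes that nobody changes after leaving. That sits badly with section 1.7, which expects eCBTi participants to improve from baseline, and with section 2.6.2, which includes the ACC to control for placebo effects and so allows for change there too.

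The analysis labelled by protocol has no adherence criterion. It is an observed-case analysis, and a report that the per-protocol and ITT results agree would mislead. At stake are the size and standard error of the primary comparison.

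**Working it through.** **Inputs from section 2.7:** partial eta-squared 0.08, alpha 0.05, power 0.95, 2 groups, 3 measurements, N = 32, 25 recruited per condition.

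**Assumed, because the article gives no values:** correlation 0.5 between visits, sphericity, SD 5, true difference in change of −4 points (4/5 = 0.80 SD), random dropout with half of it before week 3 and half after, and half of the change reached by week 3. Simulations used 25 per arm and 4,000 trials per scenario. They test the baseline-to-week-6 contrast, not the full three-visit interaction.

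**1. The plan's own figure.** f² = 0.08/0.92 = 0.0870, so f = 0.295. For the Group × Time test, λ = f²·N·m/(1 − ρ) = 0.0870 × 32 × 3/0.5 = 16.7, with 2 and 60 degrees of freedom. Power is 0.955, so N = 32 reproduces. The sample size is not in dispute.

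**2. Room for missing data.** (25 − 16)/25 = 36%. This is the largest loss that still leaves 16 per condition.

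**3. Filling with the overall sample mean.** With equal loss p, filled participants of both arms receive the same value and contribute no difference. The expected difference is (1 − p)·δ. At p = 0.36: 0.64 × 0.80 = 0.51 SD.

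**4. LOCF.** Half of the dropouts keep the baseline score (no effect) and half keep the week 3 score (half the effect). The expected difference is δ·[(1 − p) + (p/2)(1/2)] = δ(1 − 0.75p). At p = 0.36: 0.80 × 0.73 = 0.58 SD.

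Simulated estimates for a true −4 points, with the formula value in brackets:

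| Loss in both arms | Observed only | Overall mean | LOCF |
|---|---|---|---|
| 10% | −4.01 | −3.62 (−3.60) | −3.73 (−3.70) |
| 20% | −4.01 | −3.19 (−3.20) | −3.39 (−3.40) |
| 36% | −4.02 | −2.55 (−2.56) | −2.94 (−2.92) |

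At 36%, coverage of the 95% interval is 94% for observed data, 83% for overall-mean filling and 87% for LOCF.

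**5. Filling with the arm mean.** At 36% loss the estimate is −4.01, but the model standard error is 1.41 against a true 1.81. Coverage is 88%, and type I error with no true effect is about 12% for a test of change. A week 6 comparison alone fares worse. With 16 of 25 observed, the apparent variance of an arm mean is s² × 15/(24 × 25) = 0.025s² against a true s²/16 = 0.0625s², a standard-error ratio of √0.4 = 0.63. A threshold of 1.96 then acts like 1.24, which is about 21% type I error; simulation gave 22–24%.

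**6. LOCF with no true effect.** If both arms improve by c, the expected false difference is 0.75·c × (gap in dropout), in favour of the arm that loses fewer.

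| c | Dropout | False difference | Type I error |
|---|---|---|---|
| 0.8 SD | 45% vs 15% | 0.75 × 0.8 × 0.30 = 0.18 SD | about 10% |
| 0.8 SD | 20% vs 10% | 0.75 × 0.8 × 0.10 = 0.06 SD | about 5% |
| 0.8 SD | 36% vs 36% | 0 | about 5% |
| 0 | 45% vs 15% | 0 | about 5% |

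Overall-mean filling did not inflate type I error: 5.2% at 36% loss in both arms.

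**The case against.** **Scope of the replacement rule.** It comes before the words that introduce the intervention study, so it may have been meant for the survey or for single items. This is a fair reading. But the sentence stands under the Intervention heading, directly after the Group × Time model, and carries no restriction. What can be said is that its scope is unclear. A reader might infer that the plan certainly fills whole visits with the pooled mean; the text does not say so.

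**Three contradictory rules for one value.** A reader might infer this too. It is too strong: the available-data analysis and LOCF are two deliberate parallel analyses. Only the replacement rule collides with them, and only if it is applied to missed visits.

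**LOCF is conservative, and observed data are reported beside it.** In the equal-dropout scenarios the bias is indeed towards no effect, and a disagreement between the two analyses would show. But the direction is not guaranteed (step 6), and observed-case results are unbiased here only because dropout was simulated as random.

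**LOCF is biased whenever dropout differs by arm.** This does not hold under no effect unless scores also change over time. With a true effect and 36% against 16% dropout, the result depends on control improvement and on which arm loses more. With the higher loss in eCBTi, LOCF gives about 0.59, 0.52 and 0.47 SD for control improvement of 0, 0.4 and 0.8 SD. With the arms reversed and controls improving by about 0.5 SD, it gives about 0.79.

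**Left to a fuller document.** Ranking the analyses and setting an attendance threshold can be left to the full protocol or SAP, and their absence is not counted here. The point rests on what the article does fix.

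**Conclusion.** The point holds in this form. The scope of mean/median replacement is undefined, and for missed visits neither reading is sound: pooled filling shrinks the effect (0.80 to 0.51 SD at 36% loss), and arm-mean filling gives false precision (type I error of roughly 12–24%, depending on the test). LOCF, the only ITT method, contradicts the change that the plan expects. It shrinks a true effect to about 0.58 SD at 36% loss in both arms. Where scores change and dropout differs widely between arms, it can also create a false difference. The by-protocol label is wrong for what is defined.

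These sizes rest on assumed SDs, effects, correlation and random dropout. The 36% is the plan's tolerance and not a forecast; at 10% loss the shrinkage is about 7% for LOCF (−3.73 of −4) and 10% for pooled filling (−3.62 of −4). If the replacement rule proves to be for single items only, the points on LOCF and on the label remain.

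**What to change.** 1. Delete mean/median replacement for missed assessments. If it is kept, limit it to single missing items under each questionnaire's scoring rule.
2. Replace LOCF as the ITT method with a likelihood-based mixed model for repeated measures that uses all observed scores of all randomised participants in their assigned arm. Name it as the primary analysis and state that it is valid under missing at random.
3. Keep LOCF at most as a sensitivity analysis, with its name corrected to last observation carried forward, or use one sensitivity analysis under missing not at random in its place.
4. Relabel the by-protocol analysis as observed-case.

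The cost is analysis wording and slightly more analysis work. The data collected and the sample size do not change. The primary result would then rely on missing at random, which the data cannot verify; a missing-not-at-random analysis would show how much depends on it.
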